### From postoperative day 7 (POD 8 to POD 30, follow-up)

Secondary endpoints and any mortality will also be evaluated during the follow-up period. The CONSORT flowchart of the trial is shown in Fig. 2.

**Fig. 2 Fig2:**
[figure not shown]
The CONSORT (Consolidated Standards of Reporting Trials) flowchart of the trial

### Data monitoring and handling of implausible values or missing values

A clinical investigator will identify implausible values. Missing continuous variables should be less than 10% and will be replaced by median. Missing values will be replaced by the mean of all plausible data (both groups) of the respective endpoint. Data monitoring is managed by an independent investigator who is not involved in the study. The progress of the study will be evaluated, and the completeness and accuracy of the data (informed consent forms, source data, CRFs, and outcome variables) will be verified.

### Statistics

Normally distributed variables will be expressed as the mean ± standard deviation and will be compared with the Student’s *t* test. Categorical variables will be compared by using the chi-squared test or Fisher’s exact test. Non-normal continuous variables will be expressed as median (interquartile range) and evaluated with the Mann–Whitney *U* test. Intention-to-treat analyses are performed to compare the composite outcome measure at 7 days in the two groups by the chi-squared test (or Fisher’s exact test as appropriate), and multiple logistic regression analysis adjusting will be performed to identify various risk factors (for the primary outcome and the pulmonary complications at POD 30). Adjusted analyses are performed with the use of robust Poisson generalized-linear-model regression for continuous outcomes and are presented as relative risks with 95% confidence intervals. A *P* value of less than 0.05 will be considered statistically significant, and all reported *P* values will be two-sided. Interim analysis of safety will be conducted after enrollment of the first 200 patients. All analyses will be conducted by using SPSS version 18.0 (SPSS, Chicago, IL, USA) software.

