### Blinding, data collection, randomization, and record-keeping

#### Selection of the participants

Researchers will be trained prior to investigation. Study data, including patient clinical characteristics, intraoperative respiratory parameters, postoperative outcomes, and laboratory tests, will be recorded in case report forms (CRFs) (Additional file 2).

An independent researcher will randomly assign the participants to the study group (standard PEEP group) and control group (low PEEP group) in a ratio of 1:1. The random sequence will be computer-generated, and participants will be allocated in numerical order with sealed opaque envelopes. The attending anesthesiologist performs anesthesia strictly in accordance with the research protocol and is also responsible for data during the preoperative, intraoperative, and post-anesthesia care unit (PACU) period. The chief surgeon performs the postoperative laboratory testing. An independent researcher will be involved in postoperative follow-up and data collection. Statistical analysis will be performed by a statistician who does not participate in the data collection. Patients, research staff, surgeons, ICU physicians, and the statistician will be unaware of the group allocation. Some preoperative characteristics and laboratory results will be automatically derived from a computer database.

The original data (CRF and relevant records) will be maintained for 10 years and then destroyed in accordance with hospital standards.

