### Time course of the study

#### Preoperative admission

Medical history, ASA physical status, BMI, 12-lead electrocardiogram (ECG), laboratory results, chest x-ray or computed tomography (CT) scan, ARISCAT (Assess Respiratory Risk in Surgical Patients in Catalonia) score (the ARISCAT study; Additional file 3), nutritional risk screening (NRS 2002 tool), and the results of echocardiography and spirometry (in cases of history of coronary artery disease or smoking) will be recorded.

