### Sample size calculation

The incidence rate of PPCs is 39% in the low PEEP group [15]. The two-tailed chi-squared test is performed, and we estimate that 188 patients are required to provide 90% power to detect a 50% relative difference between the two groups (39% to 20%), and type I error probability was 0.05. Given that the follow-up lost rate is 10%, 208 cases in total are needed. Analysis is computed by using G-Power (version 3.1; Informer Technologies, Inc. Universität Kiel, Germany).

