There is an increasing number of highly qualitative randomized controlled trials regarding intraoperative mechanical ventilation and PPCs in both abdominal surgeries [10, 11] and laparoscopic surgeries [32], whereas direct assessment of the effect in patients undergoing robot-assisted laparoscopic radical resection for bladder cancer or prostate cancer is still lacking. The potential significance of this trial is that it may provide evidence of the effects of intraoperative PEEP on PPCs in patients undergoing robot-assisted laparoscopic radical resection for bladder cancer or prostate cancer.

There are some potential strengths of the present trial protocol. First, the included patients will undergo elective robot-assisted laparoscopic radical resection for bladder cancer or prostate cancer with longer anesthesia duration, which is a potential risk factor for PPCs [7]. Second, this trial design includes instructions for fluid management standardization and analgesic treatments during the perioperative period. Third, the adopting ARISCAT score is considered the most valuable tool for predicting PPCs, although various scores have been developed for predicting PPC incidence based on various countries and surgical populations [9].

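### The primary test of 7-day PPC is unadjusted although ARISCAT is recorded before surgery, and no adjusted treatment estimate is assigned to this binary endpoint

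*Protocol article*

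**What the plan says.** **Primary comparison (Statistics).** "Intention-to-treat analyses are performed to compare the composite outcome measure at 7 days in the two groups by the chi-squared test", with Fisher's exact test where appropriate. Neither test uses a covariate.

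**Other models (Statistics).** A multiple logistic regression is planned for the primary outcome and for pulmonary complications at day 30. Its stated purpose is to identify risk factors. The next sentence plans adjusted analyses by robust Poisson regression, reported as relative risks with 95% confidence intervals, and assigns them to continuous outcomes. Neither sentence names a covariate.

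**Baseline predictor.** The Preoperative admission section lists the "ARISCAT (Assess Respiratory Risk in Surgical Patients in Catalonia) score" among the items recorded. The Discussion counts it as a strength of the design: "the adopting ARISCAT score is considered the most valuable tool for predicting PPCs".

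**Population.** The Background names two operations, robot-assisted prostatectomy (RALP) and cystectomy (RARC), and both are enrolled in one trial.

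**Sample size calculation.** "The incidence rate of PPCs is 39% in the low PEEP group", against 20% with standard PEEP. "The two-tailed chi-squared test is performed", and "type I error probability was 0.05". The section states that 188 patients give 90% power, raised to 208 for 10% loss.

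**The concern.** The plan identifies the variable it regards as the best predictor of its primary endpoint, collects it before surgery, and then leaves it out of the comparison that decides the trial. For a binary outcome, adjusting for a prognostic baseline variable usually raises the power of the treatment test. It also removes the effect of chance imbalance in that variable.

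The two regression sentences do not close the gap. The first is a search for risk factors. The second has the right form, a relative risk with its interval, but is attached to the wrong type of outcome: a relative risk describes a binary endpoint, and the primary endpoint is binary. Read literally, it does not cover 7-day PPC.

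At stake is some power and precision in a trial that has less power than it states. The validity of the primary test is not at stake.

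**Working it through.** **1. Inputs from Sample size calculation.** p1 = 0.39, p2 = 0.20, two-sided alpha 0.05, stated power 90%, 188 evaluable (94 per arm), 208 enrolled (104 per arm).

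**2. The plan's own figure.** With pooled variance under the null and p̄ = (0.39 + 0.20)/2 = 0.295:

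- Null term: √(2 × 0.295 × 0.705) = 0.6449
- Alternative term: √(0.39 × 0.61 + 0.20 × 0.80) = 0.6308
- n per arm for 90% power = (1.960 × 0.6449 + 1.2816 × 0.6308)² / 0.19² = 2.0725² / 0.0361 = 119, so 238 in total

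The stated 188 is not reproduced. Power at the stated size:

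- 94 per arm: z = (0.19 × √94 − 1.960 × 0.6449) / 0.6308 = 0.916, power 82.0%
- 104 per arm (no losses): z = 1.068, power 85.7%

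**3. What adjustment adds.** The article gives no figure for how well ARISCAT predicts PPC in these patients, so its strength is an assumption. I simulated 10,000 trials per setting with 94 per arm. Marginal risks were held at 39% and 20%, with one standard normal covariate standing in for ARISCAT and two-sided 0.05 tests. The logistic column is the Wald test of the treatment coefficient; the Poisson column uses the sandwich variance. The c-statistic is the covariate's alone, in the low PEEP arm.

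| Log-odds per SD | c-statistic | Chi-squared | Robust Poisson | Logistic |
|---|---|---|---|---|
| 0 (useless) | 0.50 | 81.5% | 80.5% | 81.3% |
| 0.5 | 0.64 | 82.9% | 83.9% | 84.4% |
| 0.8 | 0.70 | 82.5% | 85.5% | 86.1% |
| 1.0 | 0.74 | 82.5% | 87.1% | 87.8% |
| 1.3 | 0.79 | 82.3% | 88.7% | 90.2% |

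The Monte Carlo standard error is about 0.4 points per entry. Gains over chi-squared:

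- Robust Poisson: −1.0, 1.0, 3.0, 4.6 and 6.4 points
- Logistic: −0.2, 1.5, 3.6, 5.3 and 7.9 points

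**4. Type I error.** With 29.5% in both arms and log-odds of 0, 0.8 and 1.3 per SD, rejection rates were 4.8% to 5.2% for all three tests. Adjustment does not buy power with a looser test.

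**5. Procedure.** I put no number on adding RALP/RARC. The article gives neither the mix of operations nor a difference in PPC risk between them.

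**The case against.** **The unadjusted test is legitimate.** Under randomisation it is valid, it matches the test used for sizing, and nothing obliges a trial to adjust for a predictor it values. All of that stands. The point is efficiency, not error.

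**Adjusted analyses are already planned.** A reader might infer that the plan uses regression only to hunt for risk factors. The document does not support that: robust Poisson adjusted analyses with relative risks are there. Tying them to continuous outcomes may well be a slip. What stands is that, as worded, they do not reach the primary endpoint and the primary test remains unadjusted.

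**A covariate list can be left to the analysis plan.** True, and its absence alone is no fault. But the article does fix the primary test, and it fixes an unadjusted one.

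**Randomisation.** A reader might infer that allocation ignores ARISCAT and procedure. The text says only: "The random sequence will be computer-generated, and participants will be allocated in numerical order with sealed opaque envelopes". It neither states nor excludes strata or blocks, and an article may leave these out. I draw no conclusion about stratification.

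**Procedure as a prognostic factor.** A reader might take the Discussion's remark on longer anesthesia as separating cystectomy from prostatectomy. It describes all included patients, so a difference between the operations is not shown.

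**The gain may be small.** It may. Excluding chronic obstructive pulmonary disease, home oxygen and ASA class above III narrows the spread of baseline risk, so ARISCAT could predict weakly here. At a c-statistic of 0.64 the gain is only 1 to 2 points.

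**Conclusion.** The point holds as a low-cost improvement. The primary comparison of 7-day PPC is fixed as unadjusted, a baseline predictor that the authors rate highest is already collected, and no adjusted treatment estimate is assigned to the binary primary endpoint.

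At 94 per arm, starting from about 82% power, the gain runs from nothing for a useless covariate to about 6 points (robust Poisson) or about 8 points (logistic) for a strong one. The cost if ARISCAT proves useless is about 1 point or less. These figures assume the plan's 39% and 20%, no further losses, and a single covariate acting linearly on the log-odds.

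It would be tempting to conclude that adjustment restores the stated 90%. The calculation does not support that: at 94 per arm, only logistic regression with a c-statistic near 0.79 gets there. Adjustment recovers part of the shortfall, and the power statement needs its own correction.

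**What to change.** Before any unblinding, and before the interim safety analysis planned after 200 patients:

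1. Define the primary analysis as a model of 7-day PPC on arm, with ARISCAT score (continuous) and planned procedure (RALP or RARC) as prespecified covariates. Use the robust Poisson model the plan already names, or logistic regression with standardisation.
2. Report the adjusted relative risk and risk difference with 95% confidence intervals.
3. Keep the chi-squared (or Fisher) test as a supportive analysis.
4. Correct the robust Poisson sentence so that it refers to binary outcomes.
5. Keep the risk-factor logistic regression as a separate, exploratory analysis.
6. Correct the power statement separately. On the stated inputs, 90% power for the unadjusted test needs 238 evaluable patients, or 238/0.9 = 265 with 10% loss.

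Items 1 to 5 cost a wording amendment and a little programming for the standardised risk difference. ARISCAT is already collected and the operation is known, so no new data are needed.

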### Study endpoints

#### Primary outcome measure

The primary endpoint is PPCs, including new atelectasis or infiltrates on a chest x-ray or CT scanning, respiratory failure defined as the need for non-invasive or invasive ventilation or partial pressure of arterial oxygen/fraction of inspired oxygen (PaO_2_/FiO_2_) of less than 300 within 7 days after surgery [21].

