#### Secondary outcome measures

Secondary outcome variables are any pulmonary complications and extrapulmonary complications as follows (Additional file 5):Intraoperative complications: pneumothorax confirmed by chest x-ray and any other complications.PPCs within 30 days after surgery. Those PPCs are scored in accordance with a grading scale ranging from 0 to 4 [22] (grade 0 representing no PPCs and grades 1 to 4 representing gradually worse forms of PPCs) within 7 and 30 days after surgery (Table 1).PPCs will also be analyzed separately (Table 1).Pneumonia is defined in accordance with criteria of the Centers for Disease Control and Prevention [23];Purulent sputum;Postoperative hypoxemia and severe hypoxemia [24];Suspected pulmonary infection is described in a previous study [15];Pulmonary infiltrate is defined in accordance with consensus guidelines [25]: chest x-ray demonstrating monolateral or bilateral infiltrate.Atelectasis, pleural effusion, and pneumothorax are identified by chest x-ray.The mCPIS is calculated as previously described [26] (Table 2).Suspected pulmonary complications [14];Requirement for postoperative ventilation (respiratory failure that requires non-invasive or invasive ventilation or both) at any time after surgery in accordance with standard criteria and clinical practice guidelines [22].Postoperative extrapulmonary complications within 30 days after surgery:Criteria for systemic inflammatory response syndrome [12]Sepsis and severe sepsis [12]Septic shock [12]Other extrapulmonary infection including surgical site infection (SSI) [27] and intra-abdominal abscessNeed for postoperative blood transfusionPostoperative surgical complications: anastomotic leakage and need for surgical re-intervention, defined in accordance with consensus criteria [28]Unexpected ICU admission or readmissionICU length of stay and hospital length of stayHospital-free days at follow-up day 30In-hospital mortality and 30-day mortality (all-cause mortality 30 days after randomization).

**Table 1 Tab1:** Grade scale for postoperative pulmonary complications

Grade scale	Detailed description
Grade 1	- Cough, dry - Microatelectasis: abnormal lung findings and temperature greater than 37.5 °C without other documented cause; results of chest radiograph indicates no new findings as compared to pre-operative result - Dyspnea, not due to other documented cause

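### The adjusted-analysis sentence attaches robust Poisson relative risks to continuous outcomes, where the estimate is a ratio of means, and leaves the binary PPC outcomes without a stated adjusted relative risk

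*Protocol article*

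**What the plan says.** All the relevant rules stand in one paragraph, the Statistics section of the protocol article.

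- **Primary comparison.** "Intention-to-treat analyses are performed to compare the composite outcome measure at 7 days in the two groups by the chi-squared test", with Fisher's exact test as the alternative.
- **Logistic regression.** "multiple logistic regression analysis adjusting will be performed to identify various risk factors". It covers the primary outcome and pulmonary complications at postoperative day 30. No effect measure is named.
- **Adjusted analyses.** These use "robust Poisson generalized-linear-model regression for continuous outcomes and are presented as relative risks with 95% confidence intervals".
- **Unadjusted continuous outcomes.** The t test or the Mann–Whitney U test, according to distribution.

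The outcome types are clear from the endpoint sections. Under Primary outcome measure, "The primary endpoint is PPCs, including new atelectasis or infiltrates on a chest x-ray or CT scanning", together with respiratory failure, within 7 days: a patient either has the composite or does not. Secondary outcome measures lists PPCs within 30 days, ICU and hospital length of stay, and hospital-free days at day 30. The section Sample size calculation sets the planning rates: "The incidence rate of PPCs is 39% in the low PEEP group", to be lowered to 20%, which it describes as a relative difference of one half.

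**The concern.** The model, the effect measure and the outcome type in the adjusted-analysis sentence do not fit together. Poisson regression with robust standard errors is a standard route to adjusted relative risks for a binary outcome. Here both the model and the measure are tied to continuous outcomes.

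Two things follow if the sentence is carried out as written:

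1. A ratio of mean lengths of stay would be reported as a relative risk. A reader would take it as a statement about the probability of some event, and no such event exists.
2. The 7-day and 30-day PPC outcomes would have no prespecified adjusted relative risk. The only multivariable model named for them is the logistic one, and its stated purpose is finding risk factors. The adjusted treatment effect on the scale used for planning would be left to a choice made later.

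This is a rule the article states, so it is not a detail merely left to a fuller document.

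**Working it through.** **Step 1: the planning effect.** Inputs from Sample size calculation: 39% in the low PEEP group and 20% in the standard PEEP group.

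- Relative risk = 0.20 / 0.39 = 0.513, a relative reduction of 1 − 0.513 = 0.487, or 49%.
- An exact halving would need 0.39 / 2 = 19.5%, so the stated 50% is a rounding.

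The trial is therefore planned on a relative-risk scale.

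**Step 2: what the stated model estimates for a continuous outcome.** With a log link, E(Y) = exp(a + b·T), where T = 1 for one arm and 0 for the other. With treatment as the only term, the fitted mean in each arm equals the sample mean in that arm, so exp(b) = mean₁ / mean₀. Covariates turn this into a ratio of conditional means. At no point does it become a ratio of probabilities.

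This was checked on one simulated data set. Assumed inputs, not in the protocol: gamma-distributed stay, shape 4, true means 10 and 9, 94 patients per arm (188 / 2).

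| Quantity | Value |
|---|---|
| exp(b), robust Poisson | 0.861 (95% CI 0.746 to 0.993) |
| Ratio of the two sample means | 0.861 |

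The assumed means and the random draw set the size of this number. The identity of the two rows does not depend on them.

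**Step 3: the same model on a binary outcome.** Counts closest to the planning rates with 94 per arm: 0.39 × 94 = 36.7, taken as 37; 0.20 × 94 = 18.8, taken as 19.

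- Robust Poisson: exp(b) = 0.514 (95% CI 0.320 to 0.825). By hand, (19/94) / (37/94) = 19/37 = 0.514. Here the label relative risk is correct.
- Logistic regression: 0.390 (95% CI 0.203 to 0.749). By hand, (19/75) / (37/57) = 0.390. This is an odds ratio.

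**Step 4: why labels matter at this event rate.** From the planning rates, the odds ratio is (0.20/0.80) / (0.39/0.61) = 0.391, against a relative risk of 0.513. Taken for a relative risk, 0.391 would imply a rate of 0.39 × 0.391 = 0.1525, about 15% where 20% was planned. With a control risk of 39% the two measures are not interchangeable, so each estimate must carry its own name.

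**The case against.** **The fault may be only a label, in a supplementary analysis.** For a non-negative outcome such as length of stay, robust Poisson regression is a usable model and its ratio of means is a legitimate estimate. The unadjusted comparisons of continuous outcomes are already suitable, and the primary test is untouched. All of this stands. It limits the severity but leaves the sentence wrong: the label it prescribes is incorrect, and the outcomes for which the label would be right are not named.

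**A reader might infer that logistic regression is the wrong model for the primary outcome and would inflate its result.** The document does not support this. Logistic regression is valid for a binary outcome, its stated role is risk factors, odds ratios are nowhere mentioned, and the primary inference is the chi-squared test. A correctly labelled odds ratio of 0.39 overstates nothing. The gap in Step 4 becomes an error only if someone reads an odds ratio as a relative risk, which the article does not say it will do.

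**A reader might also infer that the ordered PPC grade is bound to an unordered test.** The grade runs from 0 to 4 ("grade 0 representing no PPCs and grades 1 to 4 representing gradually worse forms of PPCs"), and the general rule says "Categorical variables will be compared by using the chi-squared test". But the article never says that the grade counts as categorical for this purpose, and the test for one secondary scale may properly be left to the analysis plan. It also gives no distribution of grades, so any loss of power would rest on invented figures.

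**Conclusion.** The adjusted-analysis sentence is wrong as written and should be corrected. Applied to continuous outcomes, it yields ratios of means published as relative risks. It also leaves 7-day and 30-day PPC without a stated adjusted relative risk, although the design effect is a relative risk of 0.51.

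The reach is limited to the adjusted analyses. The primary chi-squared test, its error rate and the logistic risk-factor analysis are not affected. The defect itself has no numerical size, being a mismatch of outcome type and effect measure; the 0.861 only illustrates it under assumed stays.

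That the authors meant binary where they wrote continuous is likely but remains an inference. The conclusion does not depend on it, because a relative risk does not describe a continuous outcome on any reading. Rating: should-fix.

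**What to change.** Replace the sentence with text to this effect:

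- Adjusted analyses of the binary outcomes, PPC within 7 days and PPC within 30 days, use Poisson regression with a log link and robust standard errors, reported as relative risks with 95% confidence intervals.
- Adjusted analyses of continuous outcomes are reported as mean differences with 95% confidence intervals or, where a log-link model is kept, as ratios of means named as such.
- Logistic regression keeps its risk-factor role, and any estimates from it are labelled odds ratios.

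Make the change before the allocation is unblinded, so that the effect measure is not chosen with results in view. The cost is wording only: no new data, no change to sample size and no change to the primary test.

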**Methods/design:**

A total of 208 patients undergoing robot-assisted laparoscopic radical resection for bladder cancer or prostate cancer will be enrolled and then randomly assigned to a standard PEEP (6–8 cm H_2_O) group and a low PEEP (≤2 cm H_2_O) group. Both groups will receive an inspired oxygen fraction of 0.50 and a tidal volume of 8 mL/kg ideal body weight. Standard perioperative fluid management standardization and analgesic treatments will be applied in both groups. The primary endpoint is postoperative pulmonary complications within 7 days after surgery. Secondary endpoints are the modified clinical pulmonary infection score, postoperative extrapulmonary complications, postoperative surgical complications, intensive care unit length of stay, hospital length of stay, and 30-day mortality.

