### Adverse events and interruption of the trial

All patients will be continuously monitored during the study, including daily visits during in-hospital and daily phone-call visits during the out-of-hospital follow-up period (until POD 30). All serious adverse, unexpected, or possibly related events will be recorded in the CRF and will be reported to the data monitoring and safety committee (DMSC). DMSC can recommend that the study should be stopped unless there is evidence that patient is safety (a between-group difference in serious adverse events or in 30-day mortality is found).

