## Trial status

The study protocol version number is V1.0 (September 10, 2018). It is first submitted to the ethics committee of Zhejiang Provincial People’s Hospital (People’s Hospital of Hangzhou Medicine College) on September 10, 2018, and finally approved on October 22, 2018 (Additional files 6 and 7). The first participant is expected to be recruited before March 2019, and the estimated completion date of recruitment is October 2021.

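### The only scheduled interim safety analysis falls at 200 of 208 patients (96% of enrolment), so it can spare at most 8 patients

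*Protocol article*

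**What the plan says.** The Statistics section plans one interim analysis, restricted to safety: "Interim analysis of safety will be conducted after enrollment of the first 200 patients". The abstract fixes the total: "A total of 208 patients undergoing robot-assisted laparoscopic radical resection for bladder cancer or prostate cancer will be enrolled". The Sample size calculation section reaches the same total from an evaluable number, "188 patients are required to provide 90% power to detect a 50% relative difference between the two groups", and an allowance for loss: "Given that the follow-up lost rate is 10%, 208 cases in total are needed".

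The section on adverse events and interruption of the trial describes a separate route. Patients are monitored continuously, with daily visits or calls to postoperative day 30. Serious, unexpected or possibly related events go to the DMSC, which can recommend stopping. The criterion given there is that "a between-group difference in serious adverse events or in 30-day mortality is found". That section schedules no comparison between groups.

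On timing, the Study design section puts the first randomisation in January 2019. The Trial status section expects the first participant before March 2019 and adds that "the estimated completion date of recruitment is October 2021". The secondary outcomes count 30-day mortality from randomisation.

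**The concern.** An interim safety analysis is useful only if its result can change what happens to patients not yet treated. The intervention here is confined to the operation, so stopping the trial cannot help anyone already operated on. A look placed when nearly everyone has been enrolled is interim in name only.

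The need for such a look follows from the protocol's own Background, which reports possible harm in both directions: more pulmonary complications in one study of low PEEP (3 cm H2O), and haemodynamic instability in a trial of high PEEP (12 cm H2O). Neither level matches a trial arm exactly, but the authors plainly do not regard either direction of harm as excluded. The timing is a stated rule, not a detail left to another document.

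**Working it through.** **Inputs.** Look after 200 enrolled (Statistics); 208 to be enrolled (abstract, Sample size calculation); 188 evaluable and 10% loss (Sample size calculation); recruitment from January 2019, or the end of February 2019 at the latest, to October 2021 (Study design, Trial status), hence about 31 to 34 months. Even accrual is my assumption, and I take 30.4 days per month.

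**The plan's own total.** 188 / (1 − 0.10) = 208.9, which agrees with the stated 208 apart from rounding up to 209.

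**Position of the look.**
- Share of enrolment: 200 / 208 = 96.2%.
- Still to enrol: 208 − 200 = 8, and 8 / 208 = 3.8%.
- Against the evaluable target: 200 / 188 = 106%.

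**Patients left if the analysis waits for the 30-day mortality of patient 200.** Rate = 208 / months; time for the last 8 = 8 / rate; enrolled during the wait = rate × 30 / 30.4.

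| Recruitment window | Rate per month | Time to enrol last 8 | Enrolled in 30 days | Left of the 8 |
|---|---|---|---|---|
| 31 months | 6.71 | 1.19 months (36 days) | 6.62 | 1.4 |
| 34 months | 6.12 | 1.31 months (40 days) | 6.04 | 2.0 |

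Once the 30 days have passed, recruitment has about 6 to 10 days to run. Data cleaning, analysis and a committee meeting would have to fit into that time, so about 0 to 2 patients could be spared.

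**If the analysis does not wait.** At the trigger, about 200 − 6.6 = 193 to 200 − 6.0 = 194 patients already have complete 30-day data, along with the serious adverse events recorded so far. A look made at once, or with recruitment paused, could spare up to all 8. That is the ceiling under any reading.

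**Earlier timings, same accrual assumption.** Patients still unenrolled once the 30-day data of the index patients are complete:

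| Look after | Unenrolled at trigger | Unenrolled 30 days later |
|---|---|---|
| 69 (one third) | 139 | 132 to 133 |
| 104 (half) | 104 | 97 to 98 |
| 139 (two thirds) | 69 | 62 to 63 |
| 200 (as planned) | 8 | 1 to 2 |

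**Does the point depend on 208 being right?** The 188 does not reproduce as stated. For 39% against 20%, two-sided alpha 0.05 and 90% power, the pooled chi-squared formula gives 119 per arm, or 238, and 188 gives about 82% power. That is a separate matter. If the total were raised accordingly, 238 / 0.90 gives 265 enrolled, and 200 / 265 = 75%, which is still late.

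**The case against.** The strongest reply is that the interim analysis is not the only safeguard. Serious events reach the DMSC as they occur, and nothing in the adverse events section ties its power to recommend stopping to the look at 200. How often it meets is a detail that an article may leave to the full protocol or a charter. All of this stands. A reader might infer from the 96% figure that no participant can be protected, or that a harmful arm would reach essentially every patient before anyone could act. The documents support neither: 8 patients are unenrolled at the trigger, and the committee may act earlier on accumulating reports.

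A second reply is that the figure of 0 to 2 rests on waiting for the last 30-day outcome. The Statistics section speaks only of enrolment, and the committee's criterion also covers serious adverse events, which are available sooner. This stands too, which is why the ceiling is 8. Uneven accrual would move the lower figure, but not above 8.

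Neither reply rescues the timing. The committee's criterion is a difference between groups. Event-by-event reports do not supply that comparison, and the only one the article schedules comes at 200.

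**Conclusion.** The scheduled interim safety analysis is too late to do its job. It can spare at most 8 of 208 patients (3.8%). Under even accrual over 31 to 34 months, and waiting for the 30-day mortality of patient 200, it can spare about 0 to 2. The ceiling follows directly from the stated numbers; the lower range depends on those two assumptions.

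The conclusion concerns the scheduled comparison, not safety oversight as a whole, which the DMSC reporting route partly provides. The defect does not bias the primary estimate, change the type I error or invalidate the final analysis. I rate it as something that should be fixed, not as a bar to proceeding.

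**What to change.** Move the safety look substantially earlier. One reasonable choice is when about half of the patients (about 104, or 52 per arm) have completed 30-day follow-up; another is two looks at about one third and two thirds. The documents do not dictate a particular number, so these are examples. In the same amendment:

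- State that no efficacy endpoint is tested at the look, so the final two-sided alpha of 0.05 needs no adjustment.
- State who prepares the unblinded comparison for the DMSC. The section on blinding keeps the statistician unaware of allocation, and the look at 200 already needs such an arrangement.
- Reconcile the Statistics section with the adverse events section, so that the committee's between-group criterion is linked to a scheduled comparison. The sentence on stopping is also garbled and needs rewording.

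The cost is a short protocol amendment, an earlier committee report, and less information at the look than 200 patients would give. No extra patients are needed.
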